### Reporting and treating adverse events

During the course of the study, researchers will record any AEs and then comprehensively evaluate the correlations between these AEs and the clinical intervention. To our knowledge, acupotomy may cause discomfort or bruising at the sites of needle insertion, nausea, or faintness after each treatment. No other serious adverse reactions caused by acupotomy have been reported to date. No harm or compensation is anticipated for trial participation. Meanwhile, if any AE occurs, the investigator will take proper measures to ensure the safety of participants; all details will be written down carefully.

### Data management and monitoring

The experimental data will be carefully entered into an electronic case report form (CRF). To guarantee the data quality, we will appoint a dependent research assistant (RA) to be responsible for the quality control during the data collection process. Participant identification and privacy information will be deleted from all study documents to protect confidentiality. All outcomes will be manually double-checked, and a second independent data entry will be conducted to promote data quality. After data storage, only researchers directly involved in the data analysis will be permitted to access to the final trial dataset. During the study, an independent data and safety monitoring board (DSMB) of the scientific research department of Fujian Provincial Hospital will be responsible for monitoring the safety, progress, study integrity, and design aspects of the trial. Drop-outs and withdrawals from the trial will be recorded throughout the intervention, and the data will be collected in the CRF and used for the final statistical analysis. No conflict of interest with the sponsors or researchers exists.

### Statistical analysis

The statistical analysis will be carried out using SAS (SAS 9.2) statistical software. All allocated subjects with available data will be analysed, i.e. on the basis of the intention-to-treat principle. The continuous variables will be presented as the means ± SDs (standard deviations) or the medians (25th to 75th centiles) and compared using the two-tailed Mann-Whitney test or Student’s *t* test, as appropriate. Categorical variables will be presented as numbers and percentages and analysed by Fisher’s exact test or the chi-squared test. Repeated measurements will be analysed using two-way ANOVA, and Tukey’s test will be used for post hoc testing. All statistical tests will be performed with a bilateral test, and *P* ≤ 0.05 will be considered as statistically significant.

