### Sample size

Based on the results of our preliminary experiments, the visual analogue scale (VAS) scores (mean difference ± SD) at rest for postoperative day 1 were 3.47 ± 1.39 in the conventional PCA group and 2.34 ± 1.21 in the acupotomy combined with PCA group. We input these data into the G-power 3.1.9.2 software (developed by the University of Düsseldorf, Germany) to calculate the sample size. We obtained a calculated effect size of 0.867 for this outcome after the intervention. A sample size of 70 participants is required to sufficiently detect a target effect size (0.8) with a type 1 error of 5% (*α* = 0.05). Therefore, 70 participants will be recruited, with 35 participants in each group.

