### Randomization and blinding

In this study, we will use SAS (SAS 9.2) statistical software to create a randomization sequence generated by an independent statistician. The randomization sequence will assign patients on the basis of a 1:1 ratio to either the intervention group (acupotomy combined with PCA group) or the control group (conventional PCA group). The allocation sequence (containing random numbers and allocation and intervention information) will be concealed from the researchers who are responsible for enrolling and assessing participants in sequentially numbered, opaque, sealed, and stapled envelopes. The project manager will evaluate the baseline information of eligible participants and then inform them of the group to which they are assigned. Study personnel involved in recruitment, screening, data collection, and data entry will be blinded to group assignments. Due to the nature of the intervention, blinding the participants is impossible.

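### The analysis set is labelled intention-to-treat but is an available-case set: missing time points, and randomised patients with no score, leave the comparison

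*Protocol article*

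**What the plan says.** The Statistical analysis section of the protocol article defines the analysis set in one sentence: "All allocated subjects with available data will be analysed, i.e. on the basis of the intention-to-treat principle". Continuous outcomes are to be compared by t test or Mann-Whitney test. For the serial scores it adds: "Repeated measurements will be analysed using two-way ANOVA, and Tukey’s test will be used for post hoc testing". The article names no method for missing scores.

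The Data management and monitoring section deals with patients who leave, and says that what was collected from them enters the closing analysis: "Drop-outs and withdrawals from the trial will be recorded throughout the intervention, and the data will be collected in the CRF and used for the".

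Under Outcome measures, the primary outcome is VAS pain at rest and on coughing at nine occasions, from the PACU to 72 h. Both arms know their allocation: "Due to the nature of the intervention, blinding the participants is impossible". The observer who records the scores is blinded.

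**The concern.** Intention-to-treat means that every randomised patient is analysed in the arm to which he or she was allocated. A set restricted to those with data keeps the second part (as allocated) but not the first (every patient). The sentence joins the two with an equating phrase, so it claims a property that the rule does not have. This is stated in the article itself. A later analysis plan could add a missing-data method, but it would start from a set already defined and labelled.

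At stake is the protection that randomisation gives. If the absence of a score is related to pain and differs between arms, the patients who remain are no longer comparable, and the report would still carry the intention-to-treat label. The outcome is self-reported pain in unblinded patients, so such a relation is possible. Nothing in the article shows that it will occur.

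**Working it through.** **1. What is lost under the stated rule.** Reading the two sections together:

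- Scores obtained before a withdrawal are kept and used (Data management and monitoring).
- A t test or Mann-Whitney test at a given time point can use only patients with a score at that time.
- A patient with no score at any time point contributes nothing.
- A two-way ANOVA for repeated measurements, if run on complete cases, drops every patient with a partial record. The article does not say whether it will be run that way.

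To show what the last item could mean, assume 2% of scores missing independently at each of the nine occasions. The share of patients with at least one gap is 1 − 0.98^9 = 0.166, about 17%. At 1% it is 8.6%, and at 5% it is 37%. These rates are assumptions.

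**2. The plan's own figures.** The Sample size section gives day-1 resting VAS scores that "were 3.47 ± 1.39 in the conventional PCA group and 2.34 ± 1.21 in the acupotomy combined with PCA group".

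- Difference: 3.47 − 2.34 = 1.13.
- Pooled SD: √[(1.39² + 1.21²)/2] = √1.6981 = 1.303.
- Effect size: 1.13/1.303 = 0.867, which agrees with the plan: "We obtained a calculated effect size of 0.867 for this outcome after the intervention".
- For the target effect size of 0.8 and two-sided α of 0.05, a t test needs 34 per arm for 90% power. The planned 35 per arm gives 91.0%. The plan does not state its power, so 90% is inferred. On that reading, 70 leaves about 2 patients of slack (70 − 68).

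**3. Illustration of selective loss.** If k of n patients with mean score v are missing from an arm with mean m, the observed mean moves by k(v − m)/(n − k). With n = 35, loss from the control arm only (m = 3.47):

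| Missing controls (assumed) | Observed control mean | Shift | Share of 1.13 |
|---|---|---|---|
| 3, averaging VAS 5 | (121.45 − 15)/32 = 3.327 | 0.143 | 13% |
| 5, averaging VAS 5 | (121.45 − 25)/30 = 3.215 | 0.255 | 23% |
| 5, averaging VAS 6 | (121.45 − 30)/30 = 3.048 | 0.422 | 37% |

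Here 121.45 = 35 × 3.47. In each row the observed benefit of acupotomy shrinks.

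The mirror case is 5 of 35 acupotomy patients lying 1.53 points above their own arm's mean, the same distance as VAS 5 lies above 3.47. Their loss lowers that arm's mean by 5 × 1.53/30 = 0.255, and the difference grows from 1.13 to 1.385. Equal loss of this kind in both arms cancels.

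**4. An extreme version.** Simulating normal scores with the planning means and SDs and removing the highest 2, 4 or 7 of 35 control scores lowers the expected difference to 0.97, 0.84 or 0.66. Power falls from about 95% to 88%, 79% or 59%. This is a worst case for loss confined to one arm, and not a forecast.

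**5. Loss unrelated to pain.** This costs precision only. With 31 or 28 per arm (about 10% or 20% lost), power at an effect size of 0.8 is 87.3% or 83.6%, against 91.0%.

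**The case against.** The strongest reply is that this is loose wording with little consequence. Withdrawn patients' data are kept. Table 1 and the Outcome measures section schedule VAS scores to 72 h with no exception for patients who stop treatment. Observation lasts three days, so loss may be small. Methods for missing data are commonly left to an analysis plan, and none is shown. A likelihood-based model also uses only observed scores, so in practice it analyses much the same set.

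Most of this stands, and it limits the point in three ways. A reader might infer that patients who withdraw are removed altogether. The Data management section says otherwise, and whole-patient loss would need a complete-case ANOVA, which is not stated. A reader might also infer that control patients with the worst pain will leave because they know they are not getting acupotomy. The article gives no rate, reason or difference between arms, and both arms are unblinded. Nor can the article be faulted for not separating stopping treatment from withdrawing consent, since that is detail a fuller document may hold.

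The reply does not rescue the label. The article defines the set and names it wrongly, and no later missing-data method makes that sentence true. It also names an ANOVA that, in one common form, discards partial records, whereas a mixed model would use them. The model cannot recover patients with no score, which is why their number must be reported and the label changed.

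**Conclusion.** The point holds as a mislabelled analysis set combined with a weaker choice of method for incomplete serial scores. Scores already collected are retained. What leaves the comparison is missing time points, randomised patients with no score and, only if the ANOVA is run on complete cases, patients with partial records.

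The size and direction of any bias cannot be known from the article. The 23% shrinkage (0.26 of 1.13) rests on three assumptions: five losses, a mean VAS of 5 among those lost, and loss confined to the control arm. It runs against acupotomy. A reader might take the point to mean that the rule favours acupotomy. The documents do not support that, because it would require loss of high-pain patients mainly from the acupotomy arm, which is equally undocumented. The sample size is not affected by correcting the definition.

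**What to change.** In the Statistical analysis section:

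1. Replace the two-way ANOVA for the VAS scores with a likelihood-based mixed model for repeated measures, with patients analysed as allocated and every observed score used. State that it assumes scores are missing at random given the observed ones.
2. Report, by arm, the number of randomised patients with no VAS score.
3. Add one sensitivity analysis for informative loss, for example giving missing scores unfavourable values and varying these by arm, so that both directions of bias are covered.
4. Describe the set as all randomised subjects with available data, analysed as allocated, and not as full intention-to-treat.

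The cost is a change of wording, one extra analysis and a less favourable label. No further patients, visits or assessments are needed.

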### Outcome measures

When patients are transferred to the PACU, vital signs (heart rate, noninvasive blood pressure, respiratory rate, and SpO_2_) will be monitored and recorded every 5 min for at least 30 min. When the patients’ vital signs are stable and they are able to communicate easily, a series of clinical-scale evaluations and analgesia will be evaluated and recorded. The primary outcome measure of this study is the postoperative pain intensity score. Pain scores (VAS) in the PACU and postoperatively at 1, 2, 4, 8, 12, 24, 48, and 72 h at rest and coughing in each group will be assessed. The VAS ranged from 0 = no pain to 10 = unbearable pain. The mean value and standard deviation will be used for descriptive analysis. The primary outcomes of this study were the resting and dynamic pain scores, which were recorded using a VAS. The secondary outcome measures are postoperative requirements for rescue analgesia, the cumulative amount of self-administered analgesics, the level of sedation (LOS), the Bruggemann comfort scale (BCS), and the functional activity score (FAS) concerning adverse effects and patient satisfaction.

The time to the first rescue analgesic use and the cumulative amount of self-administered analgesics in the first 48 and 72 h will be recorded. The BCS, LOS, and FAS will be recorded at 1, 4, 8, 16, 24, 48, and 72 h after surgery. The LOS is recorded on a 5-point scale, with 0 indicating fully awake, 1 indicating drowsy/closed eyes, 2 indicating asleep/easily aroused with light tactile stimulation or a simple verbal command, 3 indicating asleep/arousable only by strong physical stimulation, and 4 indicating unarousable. The BCS is scored as 0, persistent pain; 1, severe pain while deep breathing or coughing; 2, mild pain while deep breathing or coughing; 3, painless while deep breathing; and 4, painless while coughing. The FAS is scored as A, not restricted; B, mild to moderately restricted; and C, severely restricted. Postoperative adverse effects such as nausea, vomiting, hypotension, hypoxemia, cardiac arrhythmia, and the complications from the drugs and technique will be recorded and treated.

Patient satisfaction will be assessed verbally at 24, 48, and 72 h after surgery using a 5-point Likert scale (5 = completely satisfied, 4 = quite satisfied, 3 = slightly dissatisfied, 2 = dissatisfied, 1 = very dissatisfied). The observer who records the postoperative data will also be blinded to the group assignments.

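### The primary pain scores are to be analysed by two-way ANOVA with Tukey's test, with no within-patient error term and no family of comparisons named; taken literally, the group test is too liberal and the per-time tests may be underpowered

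*Protocol article*

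**What the plan says.** Under Outcome measures, the primary outcome is pain intensity: "Pain scores (VAS) in the PACU and postoperatively at 1, 2, 4, 8, 12, 24, 48, and 72 h at rest and coughing". That is nine times for each of two scores, and no single time is named as primary.

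The Statistical analysis section first gives the tests for continuous variables, which will be "compared using the two-tailed Mann-Whitney test or Student’s *t* test, as appropriate". Repeated data then get a sentence of their own: "Repeated measurements will be analysed using two-way ANOVA", with Tukey's test as the post hoc procedure. The analysis set is defined as follows: "All allocated subjects with available data will be analysed, i.e. on the basis of the intention-to-treat principle". Tests are two-sided at 5%.

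The Sample size section rests on one comparison: resting VAS on postoperative day 1, 3.47 ± 1.39 against 2.34 ± 1.21, a calculated effect size of 0.867, a target of 0.8, and 35 patients per group. It states no power.

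**The concern.** The sentence on repeated data is the only one written for the shape of the primary outcome, so it carries the main conclusion. A two-way ANOVA with factors group and time, and nothing for the patient, treats nine scores from one person as nine independent people. The treatment effect is then judged against an error term that is too small for a comparison between patients.

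Tukey's test is built for all pairwise differences within a family. If the family is every group-by-time cell, most of the correction is spent on pairs that nobody needs, such as one group at 1 h against the other at 72 h.

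Two things are at stake: a false claim of benefit from the overall group test, and a missed benefit at the time on which the trial was sized.

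**Working it through.** **Inputs from the protocol.** 2 groups of 35; 9 times; two-sided 5%; pilot means and SDs as above; target d = 0.8.

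**Assumption.** The within-patient correlation ρ is not given. I take 0.2 to 0.7, equal between all pairs of times, with equal variance σ² at each time.

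**1. The protocol's own figure.** Pooled SD = √((1.39² + 1.21²)/2) = √1.698 = 1.303, and d = 1.13/1.303 = 0.867, as stated. A two-sided t test at d = 0.8 needs 34 per group for 90% power, so 70 in total is consistent with that. With 35 per group the implied power is 91.0% (94.7% at 0.867).

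**2. Group test without a patient term.** There are 70 × 9 = 630 scores and 18 cells, leaving 612 residual df. Under the null:
- Expected group mean square: σ²(1 + 8ρ).
- Expected residual mean square: σ²[68(1 + 8ρ) + 544(1 − ρ)]/612 = σ².

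The F ratio is therefore inflated by 1 + 8ρ. The type I error is close to 2[1 − Φ(1.964/√(1 + 8ρ))], and simulation agrees:

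| ρ | 1 + 8ρ | Type I error, group | Type I error, group by time |
|---|---|---|---|
| 0.2 | 2.6 | 22% | 1.3% |
| 0.3 | 3.4 | 29% | 0.5% |
| 0.5 | 5.0 | 38% | 0.02% |
| 0.7 | 6.6 | 45% | 0% |

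With first-order autoregressive correlation of 0.5, 0.7 and 0.9, the group test rejects 22%, 33% and 45%. With patient as the error stratum (68 df) it rejects about 5% at every ρ tried.

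**3. Group-by-time test.** Its expected mean square under the null is σ²(1 − ρ), set against σ², so it is conservative. What that costs depends on the pattern of effect:
- d = 0.8 at the first five times and 0 afterwards: power is still 96% to 98%.
- d rising evenly from 0 to 0.8 over the nine times: the noncentrality is 17.5 × 0.6/(1 − ρ), which is 13.1 at ρ = 0.2 and 35 at ρ = 0.7. Power is about 53% and 25% without a patient term, against 72% and over 99% with the within-patient error on 544 df.

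**4. Tukey's test over all cells.** 2 × 9 = 18 cells give 18 × 17/2 = 153 pairs, of which 9 compare the groups at the same time. The studentized range quantile is 4.955 (18 means, 612 df), so the critical t is 4.955/√2 = 3.50, a per-pair level of about 0.0005. The noncentrality for one time is 0.8 × √17.5 = 3.35. Power:

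| Method for one same-time contrast | d = 0.8 | d = 0.867 |
|---|---|---|
| Single pre-specified test | 91% | 95% |
| Bonferroni over the 9 contrasts | 68% | 77% |
| Tukey over 153 pairs | 44% | 55% |

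**The case against.** The strongest reply is that a sentence about repeated measurements, set apart from the t and Mann-Whitney tests, is shorthand for two-way repeated-measures ANOVA, and that the error term belongs in a fuller document. That reading is fair, and under it the inflation of the group test vanishes. A reader might infer that the plan certainly treats repeats as independent, but the text does not settle this.

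A reader might also infer that half the planned power is lost. The documents do not support that as a fact. The Tukey family is undefined: on the two-level group factor alone it is one comparison with no penalty, and t tests are listed and could serve at single times. The 91% is implied, not planned. Under equal variances the literal model's standard error for a same-time contrast is sound, so any loss there comes from multiplicity alone.

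Two further inferences fail:
- **An almost powerless interaction test.** The 1.3% to 0% are rejection rates under the null. Step 3 shows power from 25% to 98%, depending on the pattern of effect.
- **A proven conflict between repeated-measures ANOVA and the available-data rule.** Only the complete-case version drops a patient for one missing score; an ANOVA with patient as a factor keeps partial records. A loss of 1 − 0.99⁹ = 8.6% to 1 − 0.98⁹ = 16.6% needs that version and an assumed 1% to 2% independent missingness per score.

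What the reply does not remove is that the article commits to a named method for the primary outcome. Whether its group test has 5% or 45% type I error depends on words it leaves out. The narrow Tukey reading has its own weakness: with two groups it adds nothing to the group test and never tests the day 1 difference.

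**Conclusion.** The concern holds in conditional form. The method fixed for the primary outcome does not determine a valid analysis. Taken literally, its group test has a type I error of about 22% to 45% for ρ of 0.2 to 0.7, and its group-by-time test is too conservative, which costs power for some patterns of effect. With a patient error term the group test keeps about 5%.

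The per-time power of 44% against 91% at d = 0.8 holds only if Tukey's test spans all 18 cells. The inflation figures rest on an assumed correlation, but even at 0.1 the error is 14%. Because a better method is available at almost no cost, the sentence should be replaced and not merely clarified.

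**What to change.** Replace the sentence on two-way ANOVA and Tukey's test along these lines:

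> Resting and coughing VAS will each be analysed with a linear mixed model for repeated measures with group, time and group by time as fixed effects. The within-patient covariance will be unstructured; if that model does not converge, a named simpler structure will be used. Degrees of freedom will follow Kenward-Roger. All available scores from randomized patients will be used, in the group as allocated. The leading contrast is the group difference in resting VAS at 24 h on postoperative day 1, with its 95% confidence interval. Group differences at the other times are pre-specified supporting contrasts.

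The fallback is needed because an unstructured 9 × 9 covariance has 9 × 10/2 = 45 parameters, estimated from 70 patients. If formal claims are wanted at other times, the plan should say how those contrasts are adjusted.

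A pre-treatment VAS covariate should be added only if the score required for eligibility (VAS ≥ 7) is recorded before treatment. Table 1 schedules no VAS before the PACU, and the PACU score is itself part of the primary outcome.

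The single leading contrast, tested alone, keeps about 91% power at d = 0.8. The cost is slightly more analysis work. No patients or visits are added, and SAS is already the named software.

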## Discussion

This prospective randomized control study aims to evaluate the effects of acupotomy combined with PCA (compared to conventional PCA) on postoperative pain, functional recovery, postoperative adverse effects, and patient satisfaction among patients undergoing VATS with poorly controlled postoperative pain. Despite the application of minimally invasive techniques, improved administration of analgesic drugs, and combined use of analgesic drugs, the postoperative pain of some patients after thoracoscopic surgery is not well controlled [22].

As a concept for a multimodal perioperative analgesic regimen, the options for postoperative analgesia must be effective with minimal side effects and aim to decrease the potentially harmful consequences of thoracic surgery on immediate and long-term patient well-being [23, 24]. Moreover, as improving patients’ recovery after surgery and reducing patients’ hospital stay are key aims of fast-track surgery, other pain-relieving strategies must be considered to complement the analgesics currently used [25–27].

PCA is a common analgesic method after thoracoscopic surgery in clinical practice [1, 28], and acupotomy is a traditional Chinese acupuncture treatment focusing on the pain treatment of clinical diseases [29, 30]. The combination of acupotomy and conventional PCA can provide new insights into complicated postoperative pain management and functional rehabilitation of patients after thoracoscopy.

In this study, we will use a combination of patient-reported subjective evaluation scales and objective statistical evaluation indicators of the effect of analgesic use to verify the effect of acupotomy combined with PCA on pain after thoracoscopy, thus increasing the reliability of the research results. In addition, early rehabilitation of postoperative limb function is also an important part of evaluating the effect of surgical treatment. In this study, the FAS scale will be used to evaluate the recovery of upper limb motor function in patients after thoracoscopic surgery. At the same time, we will also focus on evaluating adverse reactions and patient satisfaction. To the best of our knowledge, this will be the first randomized controlled trial to study the effect of a combination of acupotomy and PCA on the management of postoperative pain and functional recovery in this population.

The major limitation of this protocol is its non-double-blind design. Nevertheless, we have taken some remedial measures to further ensure the quality of the research. For instance, patients will be allocated using a computerized randomization schedule to receive either of two techniques, which may control for selection bias. Moreover, the outcome assessors and statistical analysts will be blind to the intervention, which may control for report bias. Another limitation of this study is that no blank control group was established to exclude the placebo effect. We will consider this issue in the next more rigorous experimental design. This study also lacks long-term follow-up observations and assessments. The 3-day continuous observation period reflects the real-world clinical practice of the observation of acute analgesia after thoracoscopy and is sufficient to confirm the clinical efficacy and safety of acupotomy combined with PCA in the short-term treatment of pain after thoracoscopy.

In conclusion, our results may offer an innovative strategy for improving postoperative pain control that could have a substantial impact on postoperative care and quality of life for patients undergoing VATS.

